#### Secondary endpoints

Specific aspects of quality of life, as measured with the physical functioning and role functioning, and symptom scales of the EORTC QLQ-C15-PAL and the Faith subscale of the FACIT-Sp-12 will be treated as secondary endpoints.

Patient empowerment is becoming more and more important, both from health care professionals’ and from patients’ perspective [45]. Reconstructing a life story and also defining life goals and intention for the future can lead to a feeling of empowerment to undertake actions which are important. We will assess patients’ empowerment with a Dutch version of the Pearlin Mastery Scale developed by Pearlin en Schooler (1978) [46]. The Pearlin Mastery Scale measures the extent to which individuals perceive themselves in control of forces that significantly impact their lives. It consists of a 7-item scale. In previous studies, the instrument yielded satisfactory psychometric properties [47,48].

Furthermore, as patients’ view on spirituality can change over time as a result of the intervention, we will measure spirituality by the Spiritual Attitude en Interests List (SAIL), developed by the Helen Dowling Institute in the Netherlands. The SAIL is a multidimensional questionnaire for studying spiritual experiences of religious and nonreligious people with good internal consistency reliability [43].

#### Tertiary endpoints

Changes in patients’ perspective on satisfaction with life will be measured by the Diener Satisfaction with Life Scale [49]. Furthermore, as feelings of anxiety and depression may arise when patients realize the limited amount of time that is left to achieve life goals, feelings of anxiety and depression will be measured by the Hospital Anxiety and Depression Scale [50]. Also, patients’ health consumption is assessed according to a shortened and for this study adapted version of the Trimbos/iMTA questionnaire for Costs associated with Psychiatric Illness (TICP) [51]. Finally, we will explore patients’ satisfaction with the intervention by a telephone interview using a study-specific topic list.

#### Background variables

Demographic data, including data on religious/spiritual background, images of God and aspects of religious salience, as well as medical data, including tumor type, time since diagnosis and previous treatments, will be collected at baseline [52].

### Sample size calculation

The primary aim of our study is to improve quality of life and spiritual wellbeing. We will conduct a mixed design measures ANOVA to detect differences between the control-group and the intervention-group over pre-, post- and follow-up measurement. To detect a small effect (effect size f = .10) with statistical power 80%, alpha 5%, and a correlation between repeated assessments of r = .63, we need a sample of 122 patients. With an expected drop out of 20%, we will include 153 patients.

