## Methods/Design

This study primarily aims to answer the following question: does an assisted structured reflection on life events and ultimate life goals of cancer patients improve quality of life? To evaluate the effect of the structured reflection we will conduct a multicenter two-armed randomized non-blinded controlled trial. Previous randomized studies on spiritual interventions in cancer patients have included patients from hospices or palliative care units [31-34]. However, spirituality is not restricted to end of life [35]. Therefore, in this study we will include patients who have been confronted with advanced cancer, but still have a life expectancy of at least half a year. The following inclusion and exclusion criteria apply:

Inclusion criteria

1. Patients ≥ 18 years of age with advanced cancer not amenable to curative treatment.

2. Life expectancy ≥ 6 months.

Exclusion criteria

1. Karnofsky Performance Score < 60.

2. Insufficient command of the Dutch language to fill out Dutch questionnaires.

3. Current psychiatric disease.

Eligible patients will be invited by their treating oncologists and asked to give written informed consent. A baseline assessment will take place in consenting patients, including an evaluation of quality of life and spiritual wellbeing. Within two weeks after the baseline assessments patients will be randomized between an intervention and a control group (care as usual) (Figure 1).

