### Endpoints

#### Primary endpoints

Two primary endpoints are distinguished. First, general quality of life as measured with the general quality of life scale of the European Organization for Research and Treatment of Cancer Quality of Life Questionnaire-Core 15 Palliative Care (EORTC QLQ-C15-PAL). The EORTC QLQ-C15-PAL is a shortened version of the EORTC QLQ-C30, which is one of the most rigorously studied and widely used health-related quality-of-life questionnaires in oncology research [38-41].

Second, spiritual wellbeing as measured by the subscale meaning/peace of the Functional Assessment of Chronic Illness Therapy - Spiritual wellbeing 12 (FACIT-Sp12). The FACIT-Sp-12 is a widely used measure and is not restricted to a particular religion and is valid and reliable [42]. The FACIT-sp-12 demonstrates good internal consistency reliability and a significant relation with quality of life in a large, multiethnic sample [43,44].

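### The planned ANOVA treats the pre-randomization baseline as an outcome level; the test is valid and the sample size is right, but adjusting for baseline would be more efficient at no cost

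*Protocol article*

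**What the plan says.** The analysis is named in the protocol article under Sample size calculation: "We will conduct a mixed design measures ANOVA to detect differences between the control-group and the intervention-group over pre-, post- and follow-up measurement". The baseline is thus a level of the repeated factor.

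The same section gives the inputs, "To detect a small effect (effect size f = .10) with statistical power 80%, alpha 5%, and a correlation between repeated assessments of r = .63", and the results: "we need a sample of 122 patients" and "With an expected drop out of 20%, we will include 153 patients".

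Methods/Design says of the baseline visit: "A baseline assessment will take place in consenting patients, including an evaluation of quality of life and spiritual wellbeing". Randomization follows within two weeks, so baseline precedes allocation. The same section puts the primary question in directional form: whether the reflection makes quality of life better. Under Primary endpoints, "Two primary endpoints are distinguished": a general quality-of-life scale and a meaning/peace subscale. No visit is singled out for either.

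**The concern.** Because baseline is measured before allocation, the arms can differ there only by chance. An ANOVA that counts baseline as an outcome in effect compares the arms on change from baseline, and so carries the full chance difference at baseline into the comparison. Regressing on baseline removes only the part of the follow-up score that baseline predicts, which leaves less residual variance whenever the correlation is below 1. The data are the same in both analyses.

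At stake is power in a trial of patients with advanced cancer that is sized to just over 80% and expects 20% dropout. A second, smaller matter is that a 2-df test says the arms differ somewhere over time. It does not in itself give one estimate that answers the directional question.

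**Working it through.** **Inputs from the article:** f = .10, alpha 5%, power 80%, r = .63, 122 evaluable, 20% dropout (Sample size calculation); 1:1 allocation (Randomization). **Assumed here:** SD 1, one common correlation between all visits, complete data on 122.

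**1. Reproduce the plan.** For a 2 × 3 group-by-time interaction, the noncentrality is λ = f²·N·m/(1 − r) = .01 × 122 × 3 / .37 = 9.89. With 2 and 2(N − 2) = 240 df, power is .806. The smallest N reaching 80% is 121, or 122 with equal arms, and 122/.8 = 152.5, so 153. Both stated figures reproduce. The between-group main effect would need 594 and two time points 148, so of these readings only the 2-df interaction over three time points including baseline fits.

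**2. Convert f to arm differences at the two follow-ups.** f² is one quarter of the variance over the three visits of the arm difference (zero at baseline).
- Sustained (0, d, d): d²/18 = .01, d = 0.424 SD.
- One visit only (0, d, 0): also d = 0.424.
- Linear (0, d/2, d): d²/24 = .01, d = 0.490.
- Crossing (0, d, −d): d²/6 = .01, d = 0.245.

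**3. Compare the covariance matrices of the two follow-ups.**
- Change from baseline (planned): (1 − r)(I + J) = [[.74, .37], [.37, .74]].
- Baseline-adjusted: (1 − r)(I + rJ) = [[.603, .233], [.233, .603]].

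Here I is the identity and J the matrix of ones. For the sum of the two effects, the eigenvalue is .37 × 3 = 1.11 as planned and .37 × (1 + 2 × .63) = .836 adjusted. For their difference it is .37 in both. Adjustment therefore gains on whatever the two visits share and changes nothing on their difference.

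**4. Noncentrality and power of the joint 2-df test**, λ = (N/4)·δ′V⁻¹δ with N/4 = 30.5. For the sustained effect, λ = 30.5 × 2 × .18/1.11 = 9.89 as planned, and 30.5 × 2 × .18/.836 = 13.13 adjusted.

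| Pattern | λ planned | power planned | λ adjusted | power adjusted |
|---|---|---|---|---|
| Sustained | 9.89 | .806 | 13.13 | .903–.907 |
| Linear | 9.89 | .806 | 12.32 | .883–.888 |
| One visit only | 9.89 | .806 | 10.70 | .832–.837 |
| Crossing | 9.89 | .806 | 9.89 | .800–.806 |

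The range reflects the choice of denominator df (N − 4 = 118, or 2(N − 3) = 238).

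**5. Other correlations.** With r = .4 the planned test has .586 against .817, .772 and .657 adjusted (sustained, linear, one visit; larger denominator df). With r = .8 it has .975 against .988, .986 and .979. The crossing pattern ties in both cases.

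**6. One adjusted contrast, the average of both follow-ups.** The residual variance is (1 + r)/2 − r² = .815 − .397 = .418, and the SE is √(4 × .418/122) = 0.117. With 1 and 119 df, power is .949 (sustained), .876 (linear), .435 (one visit) and .050 (crossing). With 80% power it detects a sustained effect of 0.331 SD, against 0.42 SD for the planned test. It falls below the planned test when the smaller follow-up effect is less than about 0.4 of the larger: .823 at a ratio of 0.4, .748 at 0.3. A simulation of 8,000 trials per pattern agreed (sustained: .810 planned, .948 averaged contrast).

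**The case against.** The planned test holds its error rate under randomization, and its comparison of changes is unbiased. The 122 and 153 are correct. A reader might infer from this point that the test is invalid or the sample size wrong; neither follows. The chance baseline difference costs precision only.

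A reader might also infer that adjustment wins under every effect pattern. It does not. For an effect that reverses between visits, λ is the same, and with the smaller denominator df power is .800 against .806.

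The averaged contrast is no free gain either. It presumes a sustained effect. The Discussion says that patients get the printed analysis along with the second questionnaire, so a delayed effect is conceivable, and that is where averaging is weak. Naming a single visit has .849 power if a 0.424 SD effect is there, but .050 if it is only at the other visit.

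Finally, the article condenses a fuller plan. A primary contrast, an estimate with its interval and a rule against choosing the favourable visit may all stand in an analysis plan not shown. Their absence here is not a fault, and the article does not support a charge of visit-picking. Nor is sensitivity to harm a defect, since a two-sided 1-df test has it too and the Discussion foresees negative experiences.

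All of this stands. What it leaves untouched is that the article does state the method, with baseline as an outcome level, and that the same 2-df question can be tested more efficiently with the same data.

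**Conclusion.** The point holds as one of efficiency. For the same joint hypothesis, adjusting for baseline is essentially never less powerful than the planned ANOVA. At the plan's inputs it raises power from .81 to about .90, .88 or .83 for a sustained, linear or one-visit effect, and ties for a crossing effect. That the planned test is the 2-df interaction is inferred from the sizing, since the article does not use those words. The figures assume a common correlation of .63, equal variances, 122 complete cases and patterns scaled to f = .10. A single pre-named contrast would answer the directional question more directly, but it is an option whose value depends on the expected time course.

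**What to change.** For each of the two primary endpoints, take the two follow-up scores as outcomes in a linear mixed model. Include the baseline score of that endpoint as a covariate, plus visit, arm and arm-by-visit, and test the arm effects at both visits jointly on 2 df. This needs no extra patients, visits or data, only a change of wording in the analysis description. The sample size can stay.

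Optionally, pre-name one adjusted contrast with a 95% confidence interval. The average of both follow-ups suits an expected sustained effect; its price is the power of .44 if the effect is at one visit. A sponsor who expects an early-only or late-only effect should keep the joint adjusted test or name the visit in advance. Naming a visit first requires the follow-up times to be reconciled: the Abstract gives one and three months after randomization, and Methods/Design (text below Figure 1) gives two and four.

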### Randomization

Randomization will be performed on-line via a secure internet facility in a 1:1 ratio by the TENALEA Clinical Trial Data Management System using randomly permuted blocks with maximum block size 4 within strata formed by nine spiritual counsellors. The researcher contacts the randomization website after patients have signed informed consent. The researcher enters the patient into the randomization program linked to the spiritual counsellor of the patients' hospital. In case in a specific hospital more than one spiritual counsellor is involved in the study a counsellor from that hospital is randomly allocated to the patient. Then the researcher receives the random treatment allocation (intervention versus control) for the patient.

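### The 80% power claimed for a small effect is power for an interaction f of .10, which here means a difference between arms of about 0.42 to 0.49 SD

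*Protocol article*

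**What the plan says.** The Sample size calculation section names the analysis: "We will conduct a mixed design measures ANOVA to detect differences between the control-group and the intervention-group" "over pre-, post- and follow-up measurement". The target is "To detect a small effect (effect size f = .10) with statistical power 80%, alpha 5" per cent, assuming "a correlation between repeated assessments of r = .63". From this follow "we need a sample of 122 patients" and, for losses, "With an expected drop out of 20%, we will include 153 patients". The Randomization section allocates "in a 1:1 ratio by the TENALEA Clinical Trial Data Management System", so the arms are equal in size.

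The section does not say which term of the ANOVA the f belongs to, and the word interaction does not appear. It gives no difference between arms in SD units or in points on either primary scale.

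**The concern.** Cohen's f has no fixed meaning until the term it describes is named. In a plain comparison of two equal groups f = d/2, so f = .10 is a difference of 0.20 SD, which is conventionally called small. In a group-by-time interaction f measures something else: the spread of the interaction residuals over all group-by-time cells, relative to the SD within a cell. The same .10 then stands for a much larger difference between the arms.

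If N was computed on the interaction scale, the word small gives readers the wrong idea of the trial's sensitivity. Nothing else in the section would correct it, because small is the only verbal description of the target. At stake is how a non-significant result on general quality of life or on meaning/peace may be interpreted.

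**Working it through.** **Inputs.** From Sample size calculation: f = .10, power 80%, alpha 5%, r = .63, m = 3 measurements, N = 122, dropout 20%. From Randomization: k = 2 arms, 1:1. From Methods/Design: baseline is assessed before randomization, so the expected difference between arms at the first measurement is zero.

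**1. Reproduce the stated N.** For the group-by-time interaction, λ = f²·N·m/(1 − r), with df1 = (k − 1)(m − 1) = 2 and df2 = (N − k)(m − 1).

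- N = 122: λ = 0.01 × 122 × 3 / 0.37 = 9.89, df 2 and 240, power 80.6%.
- N = 120: λ = 9.73, power 79.9%.
- The smallest N is 121, or 122 with equal arms. Dropout: 122 / 0.8 = 152.5, rounded up to 153.

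Both stated figures reproduce.

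**2. Try the other readings.**

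| Reading of f = .10 | N for 80% power |
|---|---|
| Group-by-time interaction, m = 3 | 121 (122 with equal arms) |
| Between-arm main effect, λ = f²·N·m/(1 + (m − 1)r) | 594 (power at 122: 24%) |
| Interaction with m = 2 | 148 |
| Interaction, λ = f²·N·m, no correlation adjustment | 323 |
| Interaction, λ = f²·(N − k)(m − 1), no correlation adjustment | 486 |

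With two groups the main effect of time has the same λ and df as the interaction, so N alone does not exclude it. It does not compare the arms, though, and comparing the arms is the stated purpose.

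**3. Convert interaction f to a difference between arms.** Let δ be the difference between arms at each time, in units of the within-time-point raw-score SD. Then f² is the mean over times of ((δ − mean δ)/2)².

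- Constant, δ = (0, d, d): mean 2d/3; half-deviations −d/3, d/6, d/6; f² = (d²/9 + d²/36 + d²/36)/3 = d²/18. With f = .10, d = 0.10 × √18 = 0.42.
- Linear, δ = (0, d/2, d): mean d/2; half-deviations −d/4, 0, d/4; f² = (d²/16 + d²/16)/3 = d²/24. With f = .10, d = 0.10 × √24 = 0.49 at the last visit.

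**4. Power of the planned omnibus interaction test at smaller differences.**

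| d (raw-score SD) | Pattern | λ at N = 122 | Power, 122 analysed | Power, 153 analysed |
|---|---|---|---|---|
| 0.20 | constant | 2.20 | 24% | 30% |
| 0.20 | linear | 1.65 | 19% | 23% |
| 0.30 | constant | 4.95 | 49% | 59% |
| 0.30 | linear | 3.71 | 38% | 47% |
| 0.42 | constant | 9.89 | 81% | 89% |
| 0.49 | linear | 9.89 | 81% | 89% |

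A simulation with 61 patients per arm and 20,000 trials per scenario gave 24.0% and 18.5% at d = 0.20, and 80.8% and 80.4% at d = 0.42 (constant) and 0.49 (linear). For 80% power at d = 0.20 this test would need about 538 (constant) to 716 (linear) analysed patients.

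**The case against.** The strongest reply is that the statement is true as printed. It claims 80% power for f = .10 with given alpha, r and number of measurements, and that claim reproduces. A reader who knows the method can convert f, and the article never says that small means 0.20 SD. This stands in part: there is no arithmetic error, and 0.20 SD is a convention brought from outside. It does not rescue the label, because the term f refers to is not named and no difference on any scale is given. The conclusion also does not depend on the 0.20 benchmark: at 0.30 SD, power with 122 analysed is still below 50%.

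A second reply is that 19–24% holds only for the omnibus test with two degrees of freedom, under the chosen patterns and with exactly 122 analysed. That is correct, but it is the test the section names. A baseline-adjusted comparison would do better at 0.20 SD: about 30% with one follow-up and about 40% with the mean of two. Both remain far below 80%.

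A reader might go further and infer that the sample size is wrong, or that patients and funders are being misled. The documents support neither. N is right for the f stated, no communication to funders is shown, consent pages were removed from the text, and nothing in the article says that a null result will be taken to exclude a small benefit.

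**Conclusion.** The concern holds as a mislabelled detectable effect, of should-fix severity. The design has 80% power for a difference between arms of about 0.42 raw-score SD sustained over both follow-ups, or 0.49 SD reached at the last one. On the two-group scale where f = .10 is called small, these are 2.1 to 2.45 times as large (0.42/0.20 and 0.49/0.20).

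The conclusion rests on three things: f belongs to the interaction (inferred, because it is the only arm-comparing term that gives 122); the arms do not differ in expectation at baseline (from the order of assessment and randomization); and the SD is the within-time-point raw-score SD, equal across times with a common correlation of .63. The 19–24% figure rests additionally on taking 0.20 SD as small.

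**What to change.** Keep N at 122, and 153 with dropout. In Sample size calculation, state that f = .10 refers to the group-by-time interaction. Replace the words describing a small effect with: a difference between arms of about 0.42 raw-score SD at both follow-ups (0.49 SD at the last visit if it grows linearly). Name the SD explicitly, because the same effect takes a different value in change-score SDs. When results are reported, do not interpret a null finding as excluding a small benefit.

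The cost is one sentence and a less favourable statement of sensitivity. Endpoints, test, sample size and conduct are unchanged.

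### The named primary analysis, a three-wave mixed-design ANOVA, drops any patient with a missing assessment unless values are imputed; a likelihood-based mixed model would keep them

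*Protocol article*

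**What the plan says.** The only analysis method in the protocol article stands under Sample size calculation: "We will conduct a mixed design measures ANOVA to detect differences between the control-group and the intervention-group over pre-, post- and follow-up measurement". The inputs there are an effect size f of 0.10, "statistical power 80%, alpha 5"%, and "a correlation between repeated assessments of r = .63". The result is "we need a sample of 122 patients", followed by "With an expected drop out of 20%, we will include 153 patients".

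The Methods/Design section describes a non-blinded trial. The first inclusion criterion reads "Patients ≥ 18 years of age with advanced cancer not amenable to curative treatment". Patients must also have a life expectancy of at least six months, and those with a Karnofsky score below 60 are excluded. Only the intervention arm has the two consultations with a counsellor. The two primary endpoints, general quality of life and the meaning/peace subscale, are patient questionnaires.

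The article gives no analysis set and no rule for missing questionnaires. A condensed article may leave both to the full protocol or SAP, and that silence is not the point here. The point is the method that it does name.

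**The concern.** A classical mixed-design ANOVA needs a value at every level of the time factor. Without imputation, a patient who completes baseline and the first follow-up but misses the second is removed entirely.

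Two things are then at stake. The first is precision, because collected first follow-up data are thrown away. The second is validity. In incurable cancer, loss may well be related to deteriorating quality of life, which is one of the primary endpoints. In a non-blinded trial with extra sessions in one arm, and with an intervention that the Discussion section itself says may provoke anxiety or depression, loss could also differ between arms. If both happen, completers in the two arms are selected differently and their comparison loses the protection of randomization.

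**Working it through.** **1. Reproduce the plan's figures.** Inputs from Sample size calculation: f = 0.10, power 80%, alpha 5%, r = 0.63, k = 2 groups, m = 3 assessments. Sphericity is assumed, as the article does not state it. For the group-by-time interaction:

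- λ = f²·N·m/(1 − r) = 0.01 × 122 × 3/0.37 = 9.89
- df1 = (k − 1)(m − 1) = 2; df2 = (N − k)(m − 1) = 240
- Power = 80.6% at N = 122 and 79.9% at N = 120, so 122 is the smallest total with equal arms.

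Two assessments would need 148 patients, and the between-group main effect would need 594. Of these three variants, only the three-assessment interaction gives 122. For loss, 122/(1 − 0.20) = 152.5, rounded up to 153. There is no arithmetic error.

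**2. Patients affected.** 0.20 × 153 = 30.6, so about 31 (153 − 122 = 31). If half of them drop out after the first follow-up (an assumption), 30.6/2 ≈ 15 patients have first follow-up data that a completer analysis discards. If all 153 gave complete data, power would be 89.1%. That is an upper bound on what an analysis keeping incomplete patients could reach.

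**3. Benchmark difference.** For an equal difference d at both follow-ups, f² = (d²/4) × (2/9) = d²/18. With f = 0.10, d = √0.18 = 0.42 SD.

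**4. Possible bias.** The article gives no loss rates by arm, so these are assumptions. Simulation: 600,000 patients per arm, correlation 0.63 between all assessments, no true effect. Drop-out is logistic with slope 1 to 1.5 per SD, and lower or worsening scores are more likely to be lost. The completer estimate is the between-arm difference in change from baseline. The likelihood estimate uses all available data.

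| Loss, control vs intervention | Timing and mechanism | Completer bias | Likelihood bias |
|---|---|---|---|
| 20% vs 20% | any of those below, same in both arms | near zero | near zero |
| 10% vs 30% | even over both intervals, on observed scores | at most about 0.06 SD | within 0.01 SD |
| 10% vs 30% | all after first follow-up, on change, slope 1.5 | about 0.16 SD at first and 0.08 to 0.09 SD at second follow-up | within 0.01 SD |
| 10% vs 30% | even split, on the unobserved current score | about 0.03 to 0.05 SD | roughly 0.06 to 0.11 SD |

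Against the benchmark, 0.16/0.42 is about 38% and 0.06/0.42 about 14%. When loss depends on the unobserved score, the likelihood bias runs to about 0.13 SD at the affected visits, depending on timing and slope. The 15 patients in step 2 belong to an even split and the 0.16 SD to late loss only, so the two figures should not be cited together.

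**The case against.** The strongest reply is that the article never says drop-outs are excluded. Dividing by one minus the drop-out rate is routine, also in trials that analyse by mixed model or imputation, and it defines no analysis set. The full protocol or SAP may provide for imputation. This stands. A reader might infer that the plan commits itself to a completer analysis and that its comparison is therefore no longer the randomized one, but the text does not support that. It supports only that the named method, used without imputation, would have this effect.

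Second, the larger bias figure needs a threefold imbalance in loss, all of it late and driven by change. Nothing in the article suggests such a pattern. The eligibility limits on life expectancy and performance status, with follow-up ending within about four months, also restrict loss through deterioration. This stands too, and it is why the bias is given as a range that starts at zero.

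Third, the likelihood model does well partly because the first three rows of the table make drop-out depend on observed scores, or equal in both arms. Where it depends on the unobserved score and differs by arm, the model was more biased than the completer change score. This is correct and limits what may be claimed for the remedy.

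None of this removes the core. The ANOVA is a stated choice, not an omitted detail, and it handles incomplete patients poorly.

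**Conclusion.** The point holds as a weakness of the named method. Without imputation, the three-wave ANOVA would leave out up to about 31 of 153 randomized patients at the plan's own drop-out rate and would waste the follow-up data they had given. The sample size itself is correct.

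Bias is a possibility whose size rests on assumed loss patterns: near zero if loss and mechanism are the same in both arms, at most about 0.06 SD for 10% versus 30% spread evenly, and about 0.16 SD at the first follow-up in the late, change-driven extreme. A reader might take the last figure as the expected bias, but the article gives no arm-specific rates that would support it. The change is worth making because it is cheap and recovers data, not because bias has been shown.

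**What to change.** Name as the primary analysis a likelihood-based mixed model for repeated measures with unstructured covariance, using every available assessment of all randomized patients in their allocated arm. Keep the three-wave ANOVA on completers as a sensitivity analysis. If the ANOVA is to remain primary, state the analysis set and how missing assessments are imputed.

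The mixed model removes the bias when drop-out depends on observed scores, but not when it depends on unobserved ones. A sensitivity analysis for that case, such as a delta adjustment, is therefore advisable, and its detail can sit in the SAP.

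The cost is analysis wording and a little programming, with no extra patients or data. The change should be fixed before outcome data are seen.
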